## Abstract

**Introduction:** Oncologists have traditionally administered the maximum tolerated doses of drugs in chemotherapy. However, these toxicity-guided doses may lead to suboptimal efficacy. CURATE.AI is an indication-agnostic, mechanism-independent and efficacy-driven personalised dosing platform that may offer a more optimal solution. While CURATE.AI has already been applied in a variety of clinical settings, there are no prior randomised controlled trials (RCTs) on CURATE.AI-guided chemotherapy dosing for solid tumours. Therefore, we aim to assess the technical and logistical feasibility of a future RCT for CURATE.AI-guided solid tumour chemotherapy dosing. We will also collect exploratory data on efficacy and toxicity, which will inform RCT power calculations.

**Methods and analysis:** This is an open-label, single-arm, two-centre, prospective pilot clinical trial, recruiting adults with metastatic solid tumours and raised baseline tumour marker levels who are planned for palliative-intent, capecitabine-based chemotherapy. As CURATE.AI is a small data platform, it will guide drug dosing for each participant based only on their own tumour marker levels and drug doses as input data. The primary outcome is the proportion of participants in whom CURATE.AI is successfully applied to provide efficacy-driven personalised dosing, as judged based on predefined considerations. Secondary outcomes include the timeliness of dose recommendations, participant and physician adherence to CURATE.AI-recommended doses, and the proportion of clinically significant dose changes. We aim to initially enrol 10 participants from two hospitals in Singapore, perform an interim analysis, and consider either cohort expansion or an RCT. Recruitment began in August 2020. This pilot clinical trial will provide key data for a future RCT of CURATE.AI-guided personalised dosing for precision oncology.

**Ethics and dissemination:** The National Healthcare Group (NHG) Domain Specific Review Board has granted ethical approval for this study (DSRB 2020/00334). We will distribute our findings at scientific conferences and publish them in peer-reviewed journals.

**Trial registration number:** NCT04522284

## Introduction

Treatment options for oncology patients are increasingly personalised with the onset of precision medicine, which enables drug selection tailored to an individual. To truly optimise the outcome, however, the treatment should also include personalised dosing (1). Faced with a trade-off between efficacy and toxicity, oncologists traditionally administer maximum tolerated dose (MTD)—the highest dose that does not cause unacceptable side effects (2), derived from Phase I trials. If patients experience toxicities, the dose is reduced according to guidelines based on population data. The key underlying assumption is that higher doses will provide greater efficacy, which many now recognize as flawed (3). Large randomised controlled trials (RCTs) show that doubling the dose of some drugs results in more frequent toxicities, which leads to dose reductions and treatment interruptions, despite no improvement in overall survival (4, 5). Conversely, other authors suggest that 30–75% of patients may be underdosed with conventional dosing strategies (6). Given the narrow therapeutic window of oncologic drugs and the 4- to 10-fold interindividual variation in pharmacokinetic clearance (7, 8), these overdosing or underdosing events result in suboptimal results: unnecessary toxicities, low efficacy and potential failure of drug development (9). The complexity of this problem increases exponentially in multi-drug regimens, with unpredictable drug-drug interactions (10, 11).

The challenge of personalised dosing has thus far been practically unsolvable because of its monumental complexity. Pharmacokinetic-based therapeutic drug monitoring and pharmacogenetic testing are promising (12–14), but have thus far not been adopted in chemotherapy drug dosing. In addition, threshold drug exposure does not necessarily correlate with threshold efficacy, particularly due to the individualised nature of patient responses to treatment. With the advent of artificial intelligence (AI), efforts are now focused on big data in pharmacogenomics (15). Though big data modelling is valuable, it is unsuitable for dynamic, multifactorial diseases, as it requires massive volumes of population information, comprehensive prior knowledge and high temporal resolution (16).

The alternative is to use small data, where only the individual's medical profile is used solely for his/her own treatment. Harnessing AI, we previously demonstrated that a quadratic surface can closely describe the relationship between drug doses and a phenotypic response in a human system (17–21). The coefficients of the second-order polynomial are unique to each individual. AI is used to map the extensive dose-response parameter space based on minimal empirical data, thus deterministically predicting the global optimum within a pre-specified safe dose range (22). Uniquely, this process is mechanism-independent and implicitly avoids the complexities stemming from the known or unknown mechanistic components, including pharmacokinetics, pharmacodynamics, pharmacogenomics, and disease biology (23, 24). These personalised profiles, which are visually represented as response surfaces, can also be scaled into higher dimensions to enable predictions for combination drug regimens (25). As such, CURATE.AI—a small data, AI-derived, indication-agnostic and mechanism-independent technology platform—could thus allow for clinically actionable personalised dosing for precision oncology and beyond. Importantly, CURATE.AI implementation is not purely computational, as it pairs prospective calibration of patient-specific responses to treatment at different drug doses with the dose optimisation process.

Predicting the optimal dose at a single point in time is only part of the challenge. The optimal dose evolves throughout the course of treatment, with the participant's response to therapy evolving due to environmental, physiologic and disease changes, including drug resistance (7). Here, CURATE.AI's ability to continually recalibrate personalised profiles allows for dynamic dose optimisation throughout treatment (23, 24). To maximise CURATE.AI's therapeutic potential, it is thus paramount to utilize a phenotypic response biomarker that can be quantified frequently. Though the gold standard for monitoring treatment response in solid tumours is the Response Evaluation Criteria in Solid Tumours (RECIST), these radiological assessments are performed at infrequent intervals after a few chemotherapy cycles, and may not reflect the entire tumour burden in situations such as widespread metastases or central necrosis (26). Blood-based tumour markers, such as carcinoembryonic antigen (CEA) and carbohydrate antigen 19-9 (CA19-9) (27–29), can be measured more frequently. However, these traditional blood biomarkers have limited sensitivity and specificity in reflecting tumour response, especially among patients whose baseline biomarker levels are in the normal range (30). Recent advances in genomic sequencing have revealed plasma circulating tumour DNA (ctDNA) as a novel biomarker of tumour burden (31). ctDNA are DNA fragments released by tumour cells, *via* apoptosis, necrosis or active secretion. These fragments contain both genetic information (such as point mutation, copy number variation) and epigenetic information (such as DNA methylation). Quantitative changes in ctDNA have been shown to be ultra-sensitive in detecting both macroscopic and microscopic tumour load (32), including in patients without raised traditional tumour markers at baseline. Therefore, serial ctDNA measurements may be more reflective of the evolving tumour response and thus appropriate for CURATE.AI.

Though CURATE.AI has already been applied in a variety of clinical settings (23–25), there are currently no prior RCTs of CURATE.AI in patients with solid tumours. Additionally, the temporal resolution of the change in the selected tumour markers, as required for CURATE.AI, has not been yet characterised. We are thus conducting this pilot clinical trial to assess the technical and logistical feasibility of a future RCT, as well as to collect exploratory data on efficacy and toxicity to enable future sample size calculations.

## Methods and Analysis

### Trial Design

The PRECISE CURATE.AI pilot trial is a single-arm, prospective pilot clinical trial for participants receiving palliative-intent chemotherapy for solid tumours. We anticipate that any feasibility concerns in the future RCT are unlikely to arise from the logistical process or participants acceptability of randomisation. Rather, the more pressing feasibility issues relate to whether CURATE.AI profiles can be created and successfully applied, and whether the recommended doses are different from the standard-of-care. Therefore, to maximise clinical experience in delivering this intervention, we will run this pilot as a single-arm study. This protocol adheres to the Consolidated Standards of Reporting Trials (CONSORT) extension for randomised pilot and feasibility trials (33).

### Study Setting and Participant Recruitment

We will recruit participants at two centres: National University Hospital (NUH) and Ng Teng Fong General Hospital (NTFGH), which both belong to the National University Health System (NUHS), Singapore. Clinical investigators will recruit patients from outpatient clinics during routine clinical reviews, weekly trial meetings or multidisciplinary tumour boards. As this is a pilot clinical trial with no precedent data, we intend to first recruit 10 patients and perform an interim analysis, which will include formal power and statistical sample size calculations. Based on these outcomes, we will consider an RCT, or an amendment of this study protocol to expand the current cohort or to include further cohorts of patients with a wider range of chemotherapy regimens or tumour markers. We will consider participants to be evaluable for the primary outcome measures only if participants are able to complete the first two cycles of chemotherapy in an uninterrupted manner. We will replace any unevaluable participants with new participants, though we will continue to monitor and report any adverse events in the unevaluable participants. We will consider replacing participants who withdraw from the study (see Supplementary Text) with new participants if we could not collect sufficient data for primary outcome assessment.

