#### CURATE.AI Calibration-Intent Dose Recommendations

For every participant, CURATE.AI will undergo an initial calibration stage (Figure 1, Steps 1–4) with the aim of generating a personalised CURATE.AI profile based on that participant data only. CURATE.AI will provide calibration-intent dose recommendations (Figure 1, Step 1) to collect data on the participant's phenotypic response (measured by tumour markers e.g., CEA, CA19-9) to a range of drug doses (Figure 1, Step 2). Any dose recommended by CURATE.AI to the clinical investigator will always be within the pre-specified safe dose range.

CURATE.AI requires a minimum of three unique data pairs (capecitabine dose and tumour marker), with one data pair collected per cycle, to generate the personalised CURATE.AI profile (Figure 1, Step 3) based on a second-order polynomial. After giving participants capecitabine at calibration-intent doses and measuring the corresponding tumour marker levels, we will analyse the data to determine if they fulfil calibration requirements. If not, CURATE.AI will make further calibration-intent dose recommendations and more data pairs will be collected until the CURATE.AI profile can be generated.

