### Sample Size

Since this is a pilot clinical trial with no precedent data, we did not perform an upfront formal sample size calculation. We intend to first recruit 10 patients and perform an interim analysis using the data generated from these participants, which will include formal power and statistical sample size calculations. Based on these outcomes, we will consider cohort expansion or an RCT.

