### Data Collection, Management, and Analysis

#### Primary Outcome Measure

The primary outcome measure (Table 1) is the percentage of participants in whom we successfully apply a CURATE.AI profile. This is the main outcome which we will use to judge the technical feasibility of a future RCT and corresponds to the first of our primary objectives. A decision on whether we “successfully apply” the CURATE.AI profile requires expert judgement and cannot be made based on a purely numerical process therefore the statistical analyses will be viewed within the broader framework of clinical relevance. An expert panel, comprising physicians and researchers not involved in the trial, will consider the following factors with careful regard for the individual circumstances of each participant: (1) based on clinical experience, judgement and established indicators, the error/variance analyzed with descriptive statistics of numerical performance measures [i.e., mean absolute error, error distribution and bias (the frequency and extent of under- and overpredicting)] is acceptable to guide clinical decisions; (2) profile can be generated sufficiently early for the participant to potentially benefit; (3) dose-dependent relationship is observed; (4) profile is actionable (i.e., fulfils the clinical investigator's pre-specified safety requirements); (5) systemic changes in the participant which require profile recalibration are rare or readily assimilated into the CURATE.AI algorithm. This is the main outcome which we will use to judge the technical feasibility of the RCT. As per the CONSORT extension statement for pilot clinical trials, we are using “the traffic light system” to define progression criteria for the RCT (33).

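### The primary percentage leaves out and replaces participants without two uninterrupted cycles, so it tends to overstate applicability for a future RCT and can move the traffic light

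*Protocol article*

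**What the plan says.** Under Study Setting and Participant Recruitment, the protocol article calls participants "evaluable for the primary outcome measures only if participants are able to complete the first two cycles of chemotherapy in an uninterrupted manner". It goes on: "We will replace any unevaluable participants with new participants, though we will continue to monitor and report any adverse events in the unevaluable participants". For participants who withdraw, replacement is only something the team will consider, "if we could not collect sufficient data for primary outcome assessment"; the article refers to its Supplementary Text on withdrawal.

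Primary Outcome Measure and Table 1 define the outcome as the percentage of participants in whom a profile is successfully applied. A panel from outside the trial judges this on five factors, one of which is that the "profile can be generated sufficiently early for the participant to potentially benefit". Table 1 sets Green above 70%, Yellow at 10–70% and Red below 10%.

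The section on calibration-intent doses states: "CURATE.AI requires a minimum of three unique data pairs (capecitabine dose and tumour marker), with one data pair collected per cycle".

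Under Sample Size: "We intend to first recruit 10 patients and perform an interim analysis using the data generated from these participants". That interim analysis is also to include the power and sample size calculations.

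Nothing in the article puts replaced participants back into the primary percentage, or says that a rate over everyone who started will be reported.

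**The concern.** The pilot asks how often a profile can be created and applied, and part of the answer is whether this happens early enough to matter. A participant whose first cycles are interrupted, or who leaves before enough data exist, is less likely to reach that point. The stated rule takes such people out of the percentage and fills their places with others who got through the first two cycles.

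Interruption is foreseeable on the article's own account. Choice of Chemotherapy Regimens says that many patients tolerate full-dose capecitabine poorly, and the eligibility criteria admit metastatic disease with ECOG status up to 2. An RCT analysed as randomised would have to carry these patients. If the pilot's rate excludes them, the Green reading, and any planning figures drawn from the same data, describe a more favourable group than the one the RCT would enrol.

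There is a second, smaller issue. Evaluability is fixed at two cycles, but the method cannot produce a profile in two cycles. For a participant who leaves after cycle 2, the article does not settle whether the outcome is a counted non-success or a replacement.

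**Working it through.** **Inputs from the article.** Initial cohort 10 (Sample Size). Green above 70% (Table 1). At least three unique pairs, one per cycle (calibration section). Three-week cycles, with capecitabine dose changed only between cycles (Choice of Chemotherapy Regimens). The cohort of 10 has no formal calculation behind it, so there is no planned figure to reproduce.

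**Assumed, because the article gives no figure.** The number replaced, *k*; the early-loss share, *d*; the true success rate among evaluable participants, *p*. Each is shown as a range or an example.

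**Step 1: successes needed for Green.** 7/10 = 70% is not above 70%, so Green with 10 evaluable participants needs at least 8 successes.

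**Step 2: rate over all who started.** With *s* successes among 10 evaluable participants and *k* replaced participants all counted as not successful, the rate is *s*/(10 + *k*).

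| Successes among 10 evaluable | Evaluable-only rate | Largest *k* that stays Green | Smallest *k* that gives Yellow |
|---|---|---|---|
| 8 | 80% | 1: 8/11 = 72.7% | 2: 8/12 = 66.7% |
| 9 | 90% | 2: 9/12 = 75.0% | 3: 9/13 = 69.2% |
| 10 | 100% | 4: 10/14 = 71.4% | 5: 10/15 = 66.7% |

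One replacement never changes the colour in these three cases.

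**Step 3: if some replaced participants would have succeeded.** Let *r* of the *k* have a profile successfully applied after all. The rate is then (*s* + *r*)/(10 + *k*), which is below *s*/10 whenever *r*/*k* < *s*/10. The evaluable-only figure thus overstates the rate as long as replaced participants do worse than retained ones. With *s* = 8 and *k* = 2, *r* = 0 gives 8/12 = 66.7% (Yellow) and *r* = 1 gives 9/12 = 75.0% (Green). The Step 2 rates are therefore lower bounds.

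**Step 4: chance of Green.** Take *p* = 0.80 as an example. The exact binomial probability of at least 8 successes in 10 evaluable participants is 0.678, and under the stated rule it does not depend on early loss. If instead the first 10 participants to start are counted, with early losses as non-successes, the success rate is *p*(1 − *d*):

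- *d* = 10%: 0.80 × 0.90 = 0.72, P(Green) = 0.438
- *d* = 20%: 0.80 × 0.80 = 0.64, P(Green) = 0.241
- *d* = 30%: 0.80 × 0.70 = 0.56, P(Green) = 0.111

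**Step 5: two cycles against three pairs.** Two cycles × one pair = at most 2 pairs, in 6 weeks. Three pairs need at least 3 cycles, or 9 weeks, so the first efficacy-driven dose comes in cycle 4 at the earliest. The extra weekly blood draws in cycles 1 and 2 do not close the gap, because the article counts one pair per cycle and holds the CURATE.AI dose fixed within a cycle. A participant can therefore meet the two-cycle condition at least one cycle before any profile can exist.

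**The case against.** The main defence is that this is a descriptive pilot of 10 people, run as a single arm to gain experience with the method. A prespecified evaluable set is a legitimate way to ask whether the technique works in those who receive enough treatment to test it. The two-cycle rule is fixed in advance, an outside panel judges success, and Yellow leads to a modified design rather than a stop. This defends reporting the evaluable-only rate. It does not defend reading RCT feasibility from that rate alone, because the RCT's patients will include the early losses.

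Three stronger readings are tempting, and the article does not support them.

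- *The two-cycle and three-pair rules contradict each other.* They do not. The evaluability rule states a necessary condition, so both can hold: someone who stops after cycle 2 may be evaluable and count as a non-success. That works against inflation. What is meant by withdrawal and by sufficient data may be set out in the Supplementary Text, which is not shown, so the lack of definitions in the article is not faulted here.
- *Every replaced participant is a failure of the platform, so the reported rate is always the true rate divided by one minus the replacement fraction.* This fails when *r* > 0 in Step 3. The rule covers any interruption in the first two cycles, calibration may continue for as long as it needs, and participation can last 12 months, so an interrupted participant might still obtain a profile. Others may leave for unrelated reasons.
- *An unblinded team chooses who is dropped.* Only the replacement of withdrawals is discretionary. Replacement under the two-cycle rule is mandatory.

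**Conclusion.** The concern holds in a limited form. A stated rule, not a detail left to another document, restricts the primary percentage to participants who complete two uninterrupted cycles and replaces the rest. The restriction is related to the outcome without being identical to it. The likely direction is upward, on the assumption that replaced participants would succeed less often than retained ones.

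The effect can be large enough to matter: two, three or five replacements would take 8, 9 or 10 successes out of 10 from Green to Yellow if none of those replaced succeeded. Fewer replacements, or some later successes among them, would leave the colour unchanged. Because no replacement rate is given, the article does not show that the light will in fact change.

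The gap between two cycles and three pairs is a mismatch to be tidied. It raises the rate only if participants who leave after cycle 2 are replaced instead of counted.

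**What to change.** In the recruitment and primary-outcome sections:

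1. Compute applicability over all participants who start cycle 1, and count as not successful anyone in whom no profile was successfully applied, whatever the reason. An interrupted participant who continues and later has a profile judged successfully applied counts as a success.
2. Read the Table 1 progression criterion from this rate.
3. Allow replacements to be enrolled as now, but keep the replaced participants in the denominator.
4. Give the evaluable-only rate as supportive, with the number of replacements and the reason for each.
5. Reconcile the two-cycle evaluability rule with the three-pair minimum, and say how a participant who leaves after cycle 2 is classified.

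The cost is wording and one further tabulation of participants already enrolled. The downside is that the headline percentage may be lower and is conservative, since it counts some losses unrelated to the platform as non-successes. The listed reasons let the reader judge how much of the gap that explains.

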### Choice of Chemotherapy Regimens

Among the different solid tumour types, gastrointestinal (GI) tumours are one example of an appropriate solid tumour type for an initial trial with CURATE.AI. This is because they are the most prevalent (34), and they also form a significant proportion of tumours with raised levels of serum tumour markers (35), which can serve as an input for CURATE.AI. Therefore, we intend to initially recruit patients with GI tumours for this pilot clinical trial, though the eligibility criteria below permit the recruitment of patients with other solid tumour types.

We chose capecitabine-containing regimens (XELOX, XELIRI and single-agent capecitabine) as capecitabine is one of the most commonly used drugs for a wide range of GI and other solid tumours (36), which facilitates recruitment. In addition, it is generally accepted that the MTD for capecitabine is not well-tolerated in a large proportion of patients (37, 38), with guidelines recommending a starting dose lower than the MTD (39). Furthermore, previous studies have established inter-ethnic differences in tolerability profiles for capecitabine (40). Therefore, patients receiving capecitabine require a personalised approach and may benefit from CURATE.AI dose guidance.

During the trial, participants will receive the treatment in 3-week cycles, according to standard dosing schedules for each regimen (**Figure 2**) (41–43). In this pilot clinical trial, CURATE.AI will only modulate capecitabine doses while the remaining drugs (oxaliplatin in XELOX, and irinotecan in XELIRI regimens) will be held constant or adjusted at the clinical investigator's discretion, as per standard-of-care. Additionally, CURATE.AI will only modulate capecitabine doses between cycles and not within a cycle. The drugs used in these regimens will be subjected to the same storage and accountability conditions as per standard-of-care institutional requirements.

